# The mesenchymal stem cells in multiple sclerosis (MSCIMS) trial protocol and baseline cohort characteristics: an open-label pre-test: post-test study with blinded outcome assessments

**DOI:** 10.1186/1745-6215-12-62

**Published:** 2011-03-02

## Abstract

**Background:**

No treatments are currently available that slow, stop, or reverse disease progression in established multiple sclerosis (MS). The Mesenchymal Stem Cells in Multiple Sclerosis (MSCIMS) trial tests the safety and feasibility of treatment with a candidate cell-based therapy, and will inform the wider challenge of designing early phase clinical trials to evaluate putative neuroprotective therapies in progressive MS. Illustrated by the MSCIMS trial protocol, we describe a novel methodology based on detailed assessment of the anterior visual pathway as a model of wider disease processes - the "sentinel lesion approach".

**Methods/design:**

MSCIMS is a phase IIA study of autologous mesenchymal stem cells (MSCs) in secondary progressive MS. A pre-test : post-test design is used with healthy controls providing normative data for inter-session variability. Complementary eligibility criteria and outcomes are used to select participants with disease affecting the anterior visual pathway.

**Results:**

Ten participants with MS and eight healthy controls were recruited between October 2008 and March 2009. Mesenchymal stem cells were successfully isolated, expanded and characterised *in vitro *for all participants in the treatment arm.

**Conclusions:**

In addition to determining the safety and feasibility of the intervention and informing design of future studies to address efficacy, MSCIMS adopts a novel strategy for testing neuroprotective agents in MS - the *sentinel lesion approach *- serving as proof of principle for its future wider applicability.

**Trial registration:**

ClinicalTrials.gov (NCT00395200).

## Background

Multiple sclerosis (MS) is the commonest neurological cause of disability in young adults, affecting over 1.3 million people worldwide. It is a chronic multifocal and multiphasic immune mediated disorder characterised pathologically by inflammatory demyelination, axonal injury and partial remyelination [1]. Although recent evidence suggests that conventional disease modifying approaches can mitigate demyelination and secondary axonal loss resulting from focal inflammation if given during a narrow therapeutic-window in nascent RR-MS,[2,3] there are currently no therapies that slow, stop, or reverse progressive axonal loss in established disease. Mesenchymal stem cells (MSCs) are recognised as a candidate in this respect due to evidence that they promote oligodendrogenesis both *in vitro *and *in vivo*,[4,5] result in functional improvement in animal models of MS,[6,7] and confer benefit in non-neurological T-cell driven autoimmune human disease [8].

Trial design for the assessment of putative neuroprotective agents in MS presents a range of challenges including the need to identify patients who will benefit from treatment as well as to provide information on the mode of action of any intervention [9]. This requires clinical trial protocols that differ from those used in the evaluation of disease-modifying therapies in terms of both participant selection and measurement(s) of efficacy. Current methods for detecting neuroprotection are limited to comparatively insensitive assessments of overall response. These composite measures risk failure to detect subtle but nonetheless meaningful effects of intervention on components of the disease process that drive cumulative disability. Therefore, neuroprotective trial design must aim to select outcomes that are informative with respect to stages of the disease other than the relapsing-remitting phase, and which demonstrate the effects of targeting both immunological and neurobiological components of the complex pathogenesis. This requires a combination of clinical outcome measures to register improved function in addition to the use of paraclinical observations and novel biomarkers that can inform on the mechanisms of therapeutic effect and detect benefits that lie below clinical thresholds. Against this background, we report the design and baseline cohort characteristics of a phase IIA trial of autologous MSC therapy as a putative neuroprotective therapy for secondary progressive MS that uses novel approaches to address these challenges. By providing a detailed methodological description, we aim to inform the development of trial design in the wider setting of neuroprotective therapies for progressive MS.

## Methods

### Trial design

The MSCIMS Trial uses an 18-month pre-test : post-test design with a single treatment of autologous mesenchymal stem cells at 12 months. A parallel cohort of normative controls was also recruited to determine inter-session variability of assessment methods.

### Trial Centres

The trial was conducted over two sites. Clinical assessments were based at the Wellcome Trust Clinical Research Facility, Cambridge, UK; imaging assessments were carried out at the UCL Institute of Neurology, London, UK.

### Trial objectives

MSCIMS aims to establish the safety and feasibility of autologous intravenous mesenchymal stem cell therapy in multiple sclerosis (phase IIA). The primary objective is to describe the safety profile over six months of intravenously administered autologous MSCs at a dose of 1 - 2 × 10^6 ^cells / kg in patients with multiple sclerosis. The secondary objective is to explore the potential efficacy over six months of intravenously administered autologous MSCs at a dose of 1 - 2 × 10^6 ^cells / kg by clinical, neurophysiological and imaging assessments.

### Participant Selection

Patients were selected on the basis of having secondary progressive MS and prior involvement of the afferent visual pathway (table 1). Given its use as an outcome measure, a lower limit for retinal nerve fibre layer (RNFL) thickness was imposed to avoid a floor effect.

**Table 1 T1:** Eligibility criteria

Clinically definite multiple sclerosis
Expanded Kurtzke Disability Status Score (EDSS) 2.0 - 6.5 inclusive
Clinical evidence of optic nerve involvement on history or examination*
Abnormal visual evoked potential from one or both eyes suggestive of demyelination
Retinal nerve fibre layer (RNFL) thickness of at least 45 microns in one eye
T_2 _lesion on MRI of optic nerve
Age 18 - 65 inclusive
Capacity to give consent
No serious underlying bleeding disorder
Not on Beta-interferon or Glatiramer acetate within six months of trial entry and not previously on other disease modifying therapies at any point

* Defined as history of optic neuritis, Unthoff's phenomenon, or optic atrophy on examination

### Recruitment

Participants were recruited from secondary care referrals in the East Anglia and North-London regions of the UK. Referral criteria were: clinically definite multiple sclerosis; Expanded Kurtzke Disability Status Score (EDSS) 2.0 - 6.5 inclusive; clinical evidence of optic nerve involvement; not on Beta interferon or Glatiramer acetate within 6 months of referral, and not previously on other disease modifying therapies at any point.

### MSC isolation, expansion, characterisation & pre-administration safety checks

In compliance with JACIE (Joint Accreditation Committee ISCT [International Society for Cellular Therapy] - EBMT [European Group for Blood and Marrow Transplantation]) requirements, normal serology was confirmed for HIV 1 & 2, Hepatitis B, Hepatitis C, HTLV 1 & 2, Syphilis, and CMV less than thirty days before bone marrow aspiration. Following demonstration of normal platelet count, PT and APTT, bone marrow aspiration was performed under local anaesthesia and sedation (with anaesthetic supervision) in an operating theatre using standard techniques.

Clinical-grade mesenchymal stem cells were generated under good manufacturing practice conditions using standard operating procedures based on the European Group for Blood and Bone Marrow Transplantation developmental committee [8]. Briefly, bone-marrow mononuclear cells were separated by density gradient centrifugation in Ficoll-Paque™ PREMIUM (GE Healthcare UK Ltd, UK) as previously described [10]. Washed cells were re-suspended in PBS/EDTA (Miltenyi Biotec Ltd, UK) and cultured in Dulbecco's modified Eagle's medium-low glucose (Invitrogen, UK) supplemented with 10% foetal bovine serum (Hyclone, Perbio Science, UK) and plated at a density of 1 × 10^8 ^cells per cell-factory (Nunc, Thermo Scientific, UK). Cultures were maintained at 37°C in a humidified atmosphere containing 5% CO_2 _in cell factories. When the cultures were near confluence (>80%), cells were detached by treatment with 0.25% trypsin-EDTA (Invitrogen, UK) and re-plated at 3.5 × 10^6 ^cells per cell factory. When 2 × 10^6 ^cells /kg (of participant) or more were obtained, MSCs were harvested and cryopreserved in 4.5% human albumin solution (BPL, UK) with Dimethyl Sulphoxide (Origen Biomedical Inc.) at a final concentration of 10%.

MSCs were characterised in accordance with International Society of Cellular Therapy (ISCT) recommendations [11]. Briefly, this included evidence of tri-lineage differentiation potential (adipocyte, chondrocyte, osteocyte) and flow cytometry assessment confirming expression of CD73, CD90, and CD105 surface molecules (>95%) and absence of CD34, CD45, CD14, and CD3 (< 2%). Release criteria of mesenchymal stem cells for clinical use included absence of contamination by pathogens (as documented by aerobic and anaerobic cultures and mycoplasma testing before release), and lack of any genomic copy number changes by 1Mb resolution BAC array comparative genomic hybridization (aCGH) performed in the Dept. of Pathology, University of Cambridge [12].

### Intervention dose, route, and administration procedures

Participants received one treatment with autologous MSCs administered intravenously at a dose of 1 - 2 × 10^6 ^cells/kg. Administration was performed as a day-case procedure following pre-medication with chlorpheniramine 10 mg, hydrocortisone 100 mg, and metoclopramide 10 mg. Cryopreserved MSCs were thawed (≤ 4 minutes) and immediately infused over 15 minutes. Administration (mean 167.2 ml, range: 89 to 246 ml) was followed by infusion of normal saline (500 ml) over 4 hours. Participants were monitored clinically for evidence of adverse reactions over a minimum of 4 hours.

### Outcome selection & assessment schedule

In order to increase power to detect efficacy through use of tailored outcomes, complementary eligibility criteria and outcome measures were selected allowing detailed assessment of participants with disease affecting the afferent visual pathway. Study of the entire visual pathway as a model of wider disease processes allows the use of clinical and paraclinical outcomes that can inform on aspects of both structure and function [13]. Participants were assessed at 12 (M-12) and 6 (M-6) months before treatment, immediately prior to treatment (M0), and at 3 (M3) and 6 (M6) months after treatment. Assessment at each time point was split into two visits with an interval of less than two weeks: clinical assessment and visual evoked potentials were performed in Cambridge, UK; MRI, optical coherence tomography (OCT), and neuro-ophthalmological assessments were performed in London, UK. In addition, patients were reviewed weekly on four occasions following treatment to assess immediate clinical response and monitor blood parameters including: full blood count, prothrombin time, accelerated partial thromboplastin time, erythrocyte sedimentation rate, serum urea & electrolytes, serum calcium and phosphate, serum albumin, bilirubin, alanine transaminase, aspartine transaminase. C-reactive protein, thyroid-stimulating hormone, complement C3 & C4, lymphocyte subsets, and serum IgG, IgA & IgM.

### Clinical outcome measures

Detailed neurological and medical history was obtained at screening and updated at each visit. Specific enquiry for adverse events was performed and participants encouraged to keep written records of interim events. Clinical outcomes assessed at each visit were: Multiple Sclerosis Impact Scale -- 29 (MSIS-29), Beck's Depression Inventory II (BDI-II), Addenbrooke's Cognitive Examination - Revised (ACE-R), Multiple Sclerosis Functional Composite (MSFC), and EDSS. Neuro-opthalmological outcomes assessed at each visit were: Visual acuity using a retro-illuminated EDTRS chart, Contrast Acuity using retro-illuminated Sloan charts, Colour vision using the Farnsworth-Munsell 100-Hue test, and Visual Fields by automated static perimetry (Humphrey field analyser, 30-2 protocol).

### MR imaging methodology

MR images were acquired using a Siemens MAGNETOM 3.0T Tim Trio scanner (Siemens, Erlangen, Germany) with a twelve-element receiver head coil. Total acquisition time was approximately 75 minutes, extended to 130 minutes for the two visits involving optic nerve diffusion tensor imaging (DTI) and functional MRI (fMRI).

#### (i) Optic nerve imaging

Optic nerve lesions were identified using a fat saturated turbo spin echo sequences acquired at two different echo times: coronal oblique, TR = 2960 ms, TE1 = 12 ms, TE2 = 71 ms, number of averages = 4, matrix size = 512 × 384, field of view (FOV) = 24 × 18 cm^2^, in-plane resolution = 0.5 × 0.5 mm^2^, 16 × 3.0 mm slices for each, acquisition time = 4 minutes per sequence.

Optic nerve area was assessed using a fat saturated short echo fast fluid attenuated inversion recovery (sTE fFLAIR) sequence with the following parameters: TR = 1830 ms, TE = 13 ms, TI = 800 ms, matrix size = 384 × 306, 22 × 18 cm^2 ^FOV, in-plane resolution = 0.60 × 0.60 mm^2^, 16 × 3 mm contiguous coronal slices, acquisition time = 13 minutes. The mean cross sectional intra-orbital optic nerve area was calculated by averaging at least four slices of the intra-orbital segment, using semi-automatic contouring with manual correction as previously described [14].

Optic nerve magnetisation transfer ratio (MTR) was assessed by acquiring 3D gradient echo sequences with and without MT pre-pulse: TR = 36 ms, TE = 3.0 ms, number of averages = 2, flip angle = 12°, matrix size = 256 × 192, FOV = 19 × 14.25 cm^2^, in-plane resolution = 0.70 × 0.70 mm^2^, 60 × 1.5 mm contiguous coronal slices, acquisition time = 16 minutes. Optic nerves were contoured from chiasm to globe on the image acquired without the MT pre-pulse using a semi-automatic threshold based method with manual correction if required. MTR maps were calculated on a voxel by voxel basis and the contours transferred to the MTR maps, allowing calculation of MTR after manual correction for mis-registration due to movement between sequences with and without the MT pre-pulse.

Optic nerve diffusion tensor imaging (DTI) was performed by acquiring 3D fat and fluid attenuated spin echo single shot echo planar sequences: TR = 6 s, TE = 84 ms, TI = 1.2 s, matrix size = 128 × 64, FOV = 15 × 7.5 cm^2^, in-plane resolution = 1.17 × 1.17 mm^2^, 16 × 4 mm contiguous coronal oblique slices, diffusion gradients were applied in six directions with b = 600 s/mm^2 ^and one b = 0 image was also acquired, number of averages = 40, acquisition time = approximately 28 minutes [15]. The seven diffusion-weighted volumes (one b_0 _plus six b = 600 s/mm^2^), were then eddy-current corrected using the FSL software library http://www.fmrib.ox.ac.uk/fsl and diffusion metrics calculated using the Camino software package http://www.camino.org.uk[16]. The DT was calculated on a voxel by voxel basis. Square regions of interest (ROI) of fixed size (2 × 2 voxels [5.5 mm^2^]) were placed on the b_0 _image, guided by maximum signal intensity and minimum standard deviation. ROIs were then applied to the calculated parameter maps in order to determine quantitative diffusion indices. Mean diffusivity (MD), axial diffusivity (AD), radial diffusivity (RD), and fractional anisotropy (FA) were calculated by averaging parameters across at least three slices per optic nerve.

#### (ii) Brain

Axial T2-Proton density (PD) weighted dual echo turbo spin echo sequences were acquired: axial, TR = 3 seconds, TE1 = 11 ms, TE2 = 101 ms, matrix size = 192 × 256, FOV = 24 × 18 cm^2^, in-plane resolution = 0.9 × 0.9 mm^2^, 48 × 3 mm contiguous slices per echo (total 96 slices), acquisition time = 4 minutes. Hyperintense lesions were contoured from the PD image using a semi-automated threshold-based method, and cross-checked with contouring of T2 weighted images.

Axial T1 weighted spin echo sequences were also acquired: TR = 710 ms, TE = 8.5 ms, matrix size = 233 × 256, FOV = 22 × 22 cm^2^, in-plane resolution = 0.9 × 0.9 mm^2^, 48 × 3 mm contiguous slices, number of averages = 2, acquisition time = 5 minutes. T1 hypointense lesions were contoured using a semi-automated threshold based method.

Brain atrophy imaging was performed by 3D T1 weighted Modified Driven Equilibrium Fourier Transform (MDEFT) gradient echo sequences:[17-19] sagittal, TR = 7.13 ms, TE = 2.33 ms, matrix size = 224 × 256, FOV = 256 × 244 mm^2^, in-plane resolution = 1.0 × 1.0 mm^2^, 176 × 1 mm contiguous slices acquired in 12 minutes. Fully automated segmentation was performed for longitudinal assessment of atrophy using Structural Image Evaluation using Normalisation of Atrophy (SIENA); single time-point brain volumes were attained using SIENAX [20].

Brain MTR measures were obtained using coronal 3D gradient echo sequences with and without MT pre-pulse: TR = 26 ms, TE = 3.0 ms, flip angle = 10°, matrix size = 256 × 160, FOV = 25 × 16 cm^2^, in-plane resolution 1.0 × 1.0 mm^2^, 208 × 1.0 mm contiguous slices, acquisition time = 20 minutes in total. The MT images with and without pre-pulse, and the MDEFT T1 images were orientated to the axial plane, re-sliced, and registered to the PD-T2 image set. MTR maps were generated from the registered data and the registered 3D T1 volumetric image segmentation performed using SPM (Version 8)[21] with and without the lesions masked using the lesion contoured PD image. These extracted brain segments were applied to mask the MTR map into grey and white matter segments. These tissue MTR maps were then refined by applying a lower threshold of 10 pu, and erosions for whole brain & grey matter (1 voxel) and white matter (2 voxels), to remove partial volume voxels. T1 lesion masks were also applied to allow generation of MTR histograms for: whole brain (WB), grey matter (GM), white matter (WM), normal-appearing grey matter (NAGM) (GM with the lesions removed), normal appearing white matter (NAWM), T2/PD-lesions, and T1 hypointense lesions. MTR histograms in controls were obtained for: WB, GM, and WM.

Functional MR imaging was performed by acquiring T2* -weighted images depicting blood oxygen level dependent (BOLD) contrast: near axial (whole brain), TR = 3940 ms, TE = 30 ms, matrix size = 64 × 64, FOV = 192 mm, slice thickness = 3 mm. Four experiments of 5 minutes duration were performed using differing visual stimulation patterns as previously described [22]. Briefly, in a five-minute experiment, the subject uses binocular vision through red-green filter goggles to view a projected monitor while lying in the scanner. A reversing checkerboard pattern was shown for sixteen-second epochs of red or green stimuli, alternating with sixteen-second epochs of no stimulation. Red and green colour patterns were presented randomly in order to avoid predictability. The red-green filters were reversed by swapping the goggles between each five-minute session (*ie*. if the first run had red filter for the right eye, this was changed to green for the second run). Monocular stimulation was achieved for each epoch by matching the colour of stimulus and filter so that the eye looking through the red filter could only see the red checkerboard pattern while the other eye was unstimulated by red (and vice versa for green). Each five-minute experiment consisted of four epochs of green and four of red, thus stimulating both eyes four times each. Attention was monitored by a manual response task in the non-stimulation epochs. Analysis was performed using Statistical Parametric Mapping software (SPM 8.0, Wellcome Trust Centre for Neuroimaging, UCL, London, UK). Images were realigned, co-registered, and normalised to the T1 volumetric image obtained at that session. Images were then smoothed, and the experimental model was specified. Effects were analysed for each eye independently.

### Data & Safety Monitoring

An independent data monitoring committee was appointed following recruitment of the first participant and instructed to review progress 4 weeks after treatment of the first three participants and at six-month intervals thereafter.

### Blinding and data analysis

Optic nerve area, optic nerve MTR, and optic nerve DTI based outcomes were assessed by observers blind to participant status (pre/post-treatment). Lesional analysis was performed shortly after image acquisition at each visit. Brain volume, brain MTR, and fMRI analyses were performed using automated methods with minimal manual corrections; blinding was not therefore performed. Group comparisons for baseline outcomes were performed by Student's t-test. Following trial completion, safety data will be analysed to assess whether the post-intervention period is associated with an increase in adverse events; and efficacy data will be analysed to assess whether the post-intervention period is associated with a difference in pre-defined outcomes. No interim analyses are planned.

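### Brain MTR is left unblinded as an automated measure, yet four of its seven regions are defined by semi-automated lesion contours for which no blinding is stated, so the title's blinding claim is delivered only in part

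*Protocol article*

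**What the plan says.** The title of the protocol article describes "an open-label pre-test: post-test study with blinded outcome assessments", without limiting this to particular outcomes.

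The section Blinding and data analysis treats the imaging outcomes in three groups:

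- Optic nerve area, optic nerve MTR and optic nerve diffusion tensor imaging (DTI) were assessed by observers who did not know whether a scan was pre- or post-treatment.
- For lesions, only the timing is given: "Lesional analysis was performed shortly after image acquisition at each visit".
- For the remaining brain measures: "Brain volume, brain MTR, and fMRI analyses were performed using automated methods with minimal manual corrections; blinding was not therefore performed".

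Section (ii) Brain, under MR imaging methodology, describes the lesion work. For T2/PD lesions: "Hyperintense lesions were contoured from the PD image using a semi-automated threshold-based method, and cross-checked with contouring of T2 weighted images". For T1 lesions: "T1 hypointense lesions were contoured using a semi-automated threshold based method". It then describes the brain MTR processing, in which tissue segmentation was run "with and without the lesions masked using the lesion contoured PD image" and T1 lesion masks were applied as well. Seven MTR histograms result in patients. Controls have three: whole brain, grey matter and white matter.

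**The concern.** The stated reason for leaving brain MTR unblinded is that it is automated. That reason is sound only if no operator judgement enters the measure. The lesion contours are an operator-guided input, and they decide which voxels count as lesion and which as normal-appearing tissue.

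The design makes this matter. Every patient is treated, M-12, M-6 and M0 precede treatment, and M3 and M6 follow it. Efficacy is judged by comparing the period after treatment with the period before. If contouring shifts, even unintentionally, once the reader knows the patient has been infused, the shift enters the pre/post contrast directly. The healthy controls cannot reveal it: they supply inter-session variability, and they have no lesion-defined histograms. At stake are the T1 and T2 lesion volumes and the lesion-defined MTR measures, all under the secondary, exploratory efficacy objective.

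**Working it through.** The document gives no figure to reproduce on this point. The check traces each imaging outcome from its processing description to the blinding statement.

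**1. Blinding status by imaging family (Blinding and data analysis)**

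| Family | Blinding stated | Reason or remark given |
|---|---|---|
| Optic nerve area, MTR, DTI | Yes | Observers blind to pre/post status |
| Brain volume, brain MTR, fMRI | No | Automated, few manual corrections |
| Brain lesions | Not stated | Timing of reading only |

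That is 3 families stated blinded, 3 stated not blinded and 1 left open.

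**2. Where the lesion contours enter (section (ii) Brain)**

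| Measure | Defined by lesion contours? |
|---|---|
| T2 and T1 lesion volumes | Yes |
| MTR of normal-appearing grey and white matter | Yes, lesions removed |
| MTR of T2/PD lesions and of T1 lesions | Yes, the lesion is the region |
| MTR of whole brain, grey matter, white matter | Not by definition |
| Brain volume | No lesion input described; segmentation called fully automated |
| fMRI | No lesion input described |

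For MTR, 2 + 2 = 4 of 7 regions depend on the contours and 3 do not. The contours set the regions applied to the MTR maps. The maps themselves come from the registered images with and without the pre-pulse.

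**3. Like against like**

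Section (i) Optic nerve imaging describes optic nerve MTR contours as semi-automatic and threshold-based, with manual correction where needed. That outcome is blinded. Lesion contouring is also semi-automated and threshold-based, and no blinding is stated. The plan thus applies two standards to one class of method.

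**4. Could a visit-by-visit reader know the treatment status?**

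The Abstract gives recruitment from October 2008 to March 2009. Assume that M-12 fell close to recruitment.

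- Last M-6 scan: March 2009 + 6 months = about September 2009.
- First M3 scan: October 2008 + 12 + 3 months = about January 2010.
- If recruitment instead ran to June 2009, the end of screening in the Results, the last M-6 scan is about December 2009, still before January 2010.

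On this assumption, and with reading soon after acquisition, every M-12 and M-6 scan (10 × 2 = 20 of 50) was read before any post-treatment scan existed. Calendar date alone would then identify those 20 as pre-treatment, even with labels removed. M0 scans of late recruits could overlap in time with M3 scans of early recruits, so for the other 30 the date is less decisive.

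**5. Brain volume**

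Section (ii) Brain calls atrophy segmentation fully automated. Blinding and data analysis says that brain volume analysis included some manual correction, made without blinding. The two statements do not agree.

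**The case against.** The strongest defence is that the article is open about what was not blinded, and that omitting masking for an automated pipeline is a reasoned choice. For brain volume, fMRI and the whole brain, grey matter and white matter histograms, this largely stands. The lesion contours do not define those measures, and the only remaining concern is manual correction made with visit known, which the article describes as small.

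It is also fair to say that the article never states that lesions were read unblinded. A reader might infer that they were, and that automation was the excuse. The text does not support this: automation is the reason given for brain volume, brain MTR and fMRI, and for lesions there is only a statement of timing. Knowledge of visit status is an inference, though a strong one given the calendar above. Likewise, semi-automated implies some operator input, but its extent is not given.

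Finally, optic nerve area, MTR and DTI, which belong to the anterior visual pathway at the heart of the sentinel lesion approach, are stated as blinded, and the primary objective is safety. This limits the weight of the point. It does not answer it: for four of the seven MTR regions the stated rationale does not fit the method described, and the plan blinds comparable contouring elsewhere.

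**Conclusion.** The point holds in a bounded form. Automation does not justify leaving brain MTR unblinded for the 4 of 7 regions defined by semi-automated lesion contours. The T1 and T2 lesion volumes share the same exposure, because they rest on the same contours and no blinding is stated. The title is broader than the methods support.

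A reader might conclude that the title's promise is not kept at all, or that most outcomes are unblinded. The documents do not support either. Blinding is delivered in part, for three optic nerve MRI families. The article's silence on clinical, evoked-potential and optical coherence tomography assessments may be filled by the full protocol, and is not counted here. Nor do the contours explain the lack of blinding for brain volume or fMRI.

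The size of any bias cannot be derived: the document gives neither reader variability nor the extent of operator input. Its direction is also unknown, since a reader aware of visit knows the pre-treatment scans as well as the post-treatment ones. The conclusion rests on two inferences: that semi-automated contouring involves reader judgement, and that reading soon after each visit lets the reader infer status. It should be corrected, but it affects exploratory efficacy only.

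**What to change.** - After M6, and assuming the scans are retained (the article does not say), have the reader who contoured the lesions re-contour them on the patient scans, 10 patients × 5 visits = 50, with visit and date removed and order randomised. Use these contours for the lesion volumes and the four lesion-defined MTR regions. The at-visit reading can remain, but not as the source of efficacy data.
- Strip visit labels before any manual correction of brain volume, brain MTR or fMRI.
- Reconcile the two descriptions of brain volume processing: fully automated, or automated with manual correction.
- Limit the blinding claim, in the title and methods, to outcomes handled blind. If re-contouring is not feasible, limit it to the optic nerve MRI outcomes among the imaging measures.

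The cost is reader time for about 50 scans and the work of removing labels. No new scans or participants are needed. The article describes the efficacy analysis as still to come after trial completion, so the masked contours can be produced before it is run.
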